## Abstract

**Background/Objectives**: Physical exercise (PE) has been shown to have positive effects on the symptoms associated with autism spectrum disorder (ASD). However, there is still no consensus on the most appropriate PE intervention model. With this in mind, we developed a program with the aim of determining the effects of PE on physical fitness, with a view to applying it as a potential treatment. **Methods**: Using an experimental methodology, this research work will recruit 18 institutionalized young people and adults who will be allocated to one of two groups, namely (i) the youth training group and (ii) the adult training group, using low-cost materials. Both intervention groups will perform 90 min of training per session, twice a week, for 12 weeks. Evaluations will be carried out at baseline and month 3. The impact of the exercise program will be assessed based on the variables of anthropometry, body composition, cardiovascular response, and cardiorespiratory fitness. **Results**: The results of this study will contribute to the development of more effective strategies, prescription recommendations, and interventions as a guarantee in future programs of better and greater adherence to PE by institutionalized individuals with ASD. **Conclusions**: In addition, we intend to make the PE program available if it promotes positive effects in the target population.

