## 2. Materials and Methods

### 2.1. Design of the Study

This protocol describes a non-randomized experimental study, following the Consolidated Standards of Reporting Trials statement [22], with the aim of evaluating the effectiveness of two combined physical capacities (aerobic capacity and muscular strength). Participants will be allocated to one of two groups: youth training (YT) or adult training (AT).

Participants will take part in a supervised PE program for 12 weeks, twice a week, for 90 min per session. All outcome measures will be collected at two different times, at baseline (time 0, baseline assessment, week 0) and at the end of the intervention (time 1, final assessment, week 12). Figure 1 shows the study design.

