### 2.2. Participants

The program will involve volunteers, comprising young people and adults who are institutionalized in a care facility located in Coimbra (Portugal), recruited using the non-probabilistic convenience method. The YG will include individuals aged 10–17, and the AG will include individuals aged 18–65. This division is based on criteria widely recognized in the literature. Adolescence (10–17 years) is a critical phase of development characterized by rapid physiological and cognitive changes [23]. The adult age group (18–65 years), on the other hand, covers a wide range of stages, from early adulthood to middle age [24]. In the first stage, there will be an individual explanation of the objectives and procedures of the study, as well as the potential benefits, risks, and time required for its development. Secondly, participants/family members/legal guardians will sign an informed consent form.

The inclusion criteria will be as follows: (i) having a certified medical diagnosis of ASD (autistic disorder, Asperger’s syndrome, or pervasive developmental disorder without other specification) according to the standards established in the DSM-5-TR [1]; (ii) ages between 10 and 65 years; (iii) a recent history of non-participation in PE programs or similar physical motor activities; (iv) success in performing movements such as running, pulling, and pushing; (v) ability to perform the assessments; and (vi) attendance at least 75% of the total 24 sessions. The exclusion criteria will be defined as follows: (i) individuals who are unable to commit for 3 months; (ii) individuals with other associated pathologies; (iii) clinical contraindications; (iv) inability to walk without support; (v) inability to communicate; (vi) failure to provide signed informed consent; and (vii) individuals over the age of 18 who do not agree to take part in the study. Specific data on socio-economic status and level of education will not be recorded.

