### 2.5. Intervention Assignment and Blindness

Once the initial assessments have been completed, the volunteers will be allocated to the two groups according to their age group. Due to the nature of the intervention, it will not be possible to randomize the sample into groups nor to “blind” participants and the principal investigator.

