### 2.6. Protocol

The program is as close as possible to the recommendations suggested by the ACSM [11], as well as the Consort Transparent Reporting Trials [27]. The combined training program can be carried out indoors or outdoors using low-cost materials (elastic bands, balls of different weights, shin pads, mats, ropes, free weights, and steps). It is assumed that not all individuals with or without institutional support can afford a gym membership, and the high financial cost of practicing PA is often one of the barriers pointed out in the literature [16,28,29]. Combined with the need to increase the duration and structure of PE programs for the population with ASD, a 12-week program was designed, with a total of 24 sessions, with the aim of working on the following physical fitness components aimed at health and well-being [11]: aerobic endurance and resistant strength. These sessions have a similar structure to that described in the protocol of the study by Toscano, Carvalho and Ferreira [30]: a preparatory phase, an activation phase, a development phase, and a return to calm. Recent studies indicate that the duration of training programs can be a crucial factor in the success of interventions involving exercise in individuals with ASD. Short-term programs may not provide enough time for physiological and psychological adaptations to occur, which may explain why some individuals do not show significant improvements. Therefore, it is essential to consider that interventions of longer duration may favor a more significant accumulation of physical benefits, such as increased endurance and muscle strength, as well as improvements in mental health, promoting more consistent and sustainable results over time [30].

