The weekly frequency of aerobic exercise followed the recommendations of the ACSM [11], with 2 sessions a week for aerobic and muscle strength exercise. This number of weekly sessions favors adaptations that lead to catabolism followed by protein anabolism, allowing lean mass to be maintained or increased [30]. The sessions will last 90 min and will take place twice a week, with recovery periods of at least 48 h, and all interventions will be guided by a physical exercise technician (PET), a psychologist, and four monitors. As far as the type of exercises is concerned, one that focuses directly on the aerobic aspect is prescribed throughout the program and, as far as muscle strength is concerned, a circuit structure is used, recruiting the main muscle groups, taking into account its ease of execution and explanation, simplifying understanding on the part of the individuals. The number of sets varies between 1 and 3, according to the ACSM [11]. Some authors have stated that in untrained individuals, both single sets and multiple sets produce similar increases in upper and lower limb muscle strength, meaning that in the initial stages, strength training, regardless of the number of sets, seems to be effective in improving muscle results [30]. The number of repetitions per set ranges from 8 to 12. The intensity is progressive throughout the program, and the stimuli and loads imposed will be continually adjusted in order to trigger the consequent adaptation processes in the body, taking into account the principle of progressive overload. The program will initially be carried out at a moderate intensity, between 50% and 60% of HRM, progressing to a range of 60%-70% of HRM until reaching a vigorous intensity between 70% and 80% of HRM. In order to monitor the groups’ adherence to the sessions or to suspend the exercise if any participant reports abnormal pain, dizziness, vomiting, or other adverse events, a record sheet will be created to be filled in at each session, representing the only “non-exercise” component utilized during the intervention.

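### Achieved attendance (at least 18 of 24 sessions) is listed as an inclusion criterion, so read as written the uncontrolled pre-post comparison would cover compliers only

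*Protocol article*

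**What the plan says.** Section 2.2 introduces its list with "The inclusion criteria will be as follows", and item (vi) of that list is "attendance at least 75% of the total 24 sessions". The other items can be checked at entry: diagnosis, age, exercise history, ability to perform the movements and the assessments. The exclusion list in the same section separately covers people who cannot commit for 3 months.

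The order of events is clear. Section 2.5 says "Once the initial assessments have been completed, the volunteers will be allocated to the two groups according to their age group". Section 2.1 says "Participants will take part in a supervised PE program for 12 weeks, twice a week, for 90 min per session", and section 2.6 confirms that "a 12-week program was designed, with a total of 24 sessions". Consent and baseline assessment therefore come before the first session.

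The Abstract gives the size: "this research work will recruit 18 institutionalized young people and adults". The Discussion states that there will be no control group. Section 3.1.11 uses the Wilcoxon test between assessment times and names no analysis population. Attendance will be recorded: section 2.6 says "a record sheet will be created to be filled in at each session". The Abstract hopes that the results will lead, in future programs, to "better and greater adherence to PE by institutionalized individuals with ASD".

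**The concern.** An inclusion criterion has to be decidable when a person enters. Item (vi) is decided by what the person does over the following 12 weeks. Anyone who falls short has by then been consented, assessed, allocated and trained, and is declared never to have been eligible.

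The participants at risk are unlikely to be a random subset. The document itself connects missed exercise with poor tolerance: section 2.6 provides for suspending exercise after pain, dizziness, vomiting or other adverse events, and section 3.1.10 foresees injury and stress symptoms. Hypotheses (i) and (ii) rest on change within each group, so no comparator passes through the same filter. Hypothesis (iii), youth against adult, is also exposed if attendance differs by age.

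Three things are at stake: an estimate that may be too favourable for the institutions, schools or clinics in which the Discussion proposes to use the program; attendance figures with a built-in floor; and a smaller sample out of a planned 18.

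**Working it through.** **1. The threshold.** Sections 2.1 and 2.6: 12 weeks × 2 sessions = 24, which reproduces the stated total. 0.75 × 24 = 18 sessions.

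**2. Is it an entry condition or a commitment?** Item (vi) refers to attendance at a proportion of the sessions. Willingness or ability to commit is already dealt with by exclusion (i). The direct reading of (vi) is attendance achieved, which is settled only during the program.

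**3. How many could be affected?** The document gives no expected attendance, so this is illustration only. If each session is attended independently with probability p, P(at least 18 of 24) is:

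| p | P(≥18) | expected kept of 18 |
|---|---|---|
| 0.70 | 0.39 | 7.0 |
| 0.80 | 0.81 | 14.6 |
| 0.90 | 0.99 | 17.9 |

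The effect runs from trivial to severe, depending on true attendance.

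**4. Shift in the mean change.** Assume that attendance propensity and change are bivariate normal with correlation ρ, and that the lowest fraction q of attenders is removed. The mean change among those kept moves by ρ·φ(z_q)/(1−q), in SDs of the change, whatever the true mean. For q = 0.25: z_q = −0.674, φ = 0.318, and 0.318/0.75 = 0.424. So ρ = 0.3 gives 0.127 and ρ = 0.5 gives 0.212.

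| removed | ρ = 0 | ρ = 0.3 | ρ = 0.5 |
|---|---|---|---|
| 10% | 0 | 0.06 | 0.10 |
| 25% | 0 | 0.13 | 0.21 |
| 40% | 0 | 0.19 | 0.32 |

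A second model gives the same pattern. It uses beta-binomial attendance with mean 70%, 80% or 90%, an assumed concentration of 4 and an assumed true change of 0.5 SD. The shift is 0.24, 0.16 or 0.09 SD at ρ = 0.3, 0.40, 0.27 or 0.15 SD at ρ = 0.5, and none at ρ = 0.

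**5. Attendance among those analysed.** It cannot be below 18/24 = 75%. In the same beta-binomial model, true means of 70%, 80% and 90% become about 88%, 91% and 94% among those kept. That the mean rises whenever anyone is removed needs no assumption; only the size does.

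**6. Loss of sample.** The document does not state the split of the 18, so assume 9 per group. Removing 25% leaves 0.75 × 9 = 6.75, about 7. Simulated power of the exact two-sided Wilcoxon signed-rank test at the 5% level, for a normally distributed change of 1.0 SD:

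| n | power |
|---|---|
| 9 | about 68% |
| 8 | about 61% |
| 7 | about 57% |
| 6 | about 36% |

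At n = 5 the smallest possible exact p is 2/2⁵ = 0.0625. Reaching 6 from 9 means removing 33%, and reaching 5 means removing 44%.

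**The case against.** The strongest reply is that the document never describes removal. Section 3.1.11 names no analysis set, sections 2.1 and 3.1.9 describe the week-12 evaluation without an attendance condition, and an analysis plan that is not shown may define the set. This stands in part: a reader might infer that low attenders are dropped from every analysis as a stated step, and the text does not say so. It does not rescue the criterion. A plan that kept low attenders would contradict section 2.2 as it now reads.

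A related reply is that (vi) is only an undertaking to attend. That is possible, but exclusion (i) already does that work.

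Secondly, a reader might infer that the effect will be overstated. The document does not establish this. The direction depends on a positive link between attendance and improvement, which is plausible for a training program but nowhere given, and with no link there is no shift. Even 0.21 SD is smaller than the standard error of a mean change with 9 people (1/√9 = 0.33 SD). That does not remove the objection, because a systematic shift does not average out, but it keeps the size in proportion.

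Thirdly, a reader might infer that reported adherence becomes meaningless. That goes too far. Adherence is not a listed outcome, the sentence in the Abstract concerns future programs, and the record sheets would hold attendance for everyone. Only a figure restricted to those analysed would have the floor.

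Fourthly, the sample loss should not be judged by the n = 6 or n = 5 rows. They need a third or more of a group to be removed, which is speculative in a supervised program for people institutionalized in a care facility. The p-value floor also applies only to exact p-values, and the document does not say which kind will be used. Nor can the power loss simply be added to the bias, since an upward shift would itself raise the rejection rate.

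**Conclusion.** The point holds as an error in what is written: an outcome of the program is used as a condition of entry. Applied literally, it turns an uncontrolled pre-post study of everyone who started into one of those who attended at least 18 sessions.

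The 18-session threshold, the impossibility of judging it at entry and the 75% floor among those retained follow from the text. The bias is a risk and not a demonstrated result: about 0.13 to 0.21 SD towards benefit if 25% are removed and the correlation is 0.3 to 0.5, both assumed, and zero if attendance and change are unrelated. The fall in power from about 68% to about 57% rests on the assumed 9 per group, 25% removed, a change of 1.0 SD and exact p-values.

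It should be corrected before the week-12 assessments, because data not collected from low attenders then cannot be recovered by any later analysis.

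**What to change.** - Remove item (vi) from the inclusion criteria in section 2.2. Exclusion (i) can stay as the prospective commitment condition.
- State that the main analysis includes every participant with a baseline assessment who starts the program.
- Attempt the week-12 assessment in all of them, whatever their attendance, and report who could not be assessed and why.
- Report the attendance distribution for all who start, from the session record sheets.
- Keep at least 75% attendance only to define a labelled per-protocol sensitivity analysis, shown beside the main result.

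The cost is a change of wording and a few extra week-12 assessments, which should be manageable because the participants are institutionalized in one care facility and attendance is recorded anyway. The estimated change may look less favourable, but it will describe everyone who was offered and started the program.

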### 2.3. Informed Consent

This research, referenced as CE/FCDEF-UC/00732021, has been submitted to and approved by the Ethics and Research Committee of the Faculty of Sports Sciences and Physical Education of the University of Coimbra (FCDEF-UC). The parents or legal guardians allowing their children to take part in the study will sign a free and informed consent form, which includes all the information about the procedures to be carried out in accordance with the Declaration of Helsinki [10,21]. In this sense, this research is within the norms provided by law for scientific research, with protection for those involved [25,26].

### 2.4. Ethics

Any changes to the protocol will be agreed upon by the research team and formally communicated to the FCDEF-UC ethics committee prior to implementation. Written informed consent will be obtained from the parents or legal guardians (who will be provided with a copy) after the study has been fully clarified (objectives, procedures, expected results, and potential risks). Each participant will then be given a code, guaranteeing their anonymity.

The database and other files inherent to the project will be stored in a secure place using appropriate technical and organizational measures. All the data collected will be used exclusively for this study. Contact with participants will be made in a private environment, and at the end of the research, they will be asked to destroy their “code cards”. In addition, all the information collected will be deleted, except for that which has implications for the conclusion of this project, which will be kept for 5 years according to research policy.

### 2.5. Intervention Assignment and Blindness

Once the initial assessments have been completed, the volunteers will be allocated to the two groups according to their age group. Due to the nature of the intervention, it will not be possible to randomize the sample into groups nor to “blind” participants and the principal investigator.

### 2.6. Protocol

The program is as close as possible to the recommendations suggested by the ACSM [11], as well as the Consort Transparent Reporting Trials [27]. The combined training program can be carried out indoors or outdoors using low-cost materials (elastic bands, balls of different weights, shin pads, mats, ropes, free weights, and steps). It is assumed that not all individuals with or without institutional support can afford a gym membership, and the high financial cost of practicing PA is often one of the barriers pointed out in the literature [16,28,29]. Combined with the need to increase the duration and structure of PE programs for the population with ASD, a 12-week program was designed, with a total of 24 sessions, with the aim of working on the following physical fitness components aimed at health and well-being [11]: aerobic endurance and resistant strength. These sessions have a similar structure to that described in the protocol of the study by Toscano, Carvalho and Ferreira [30]: a preparatory phase, an activation phase, a development phase, and a return to calm. Recent studies indicate that the duration of training programs can be a crucial factor in the success of interventions involving exercise in individuals with ASD. Short-term programs may not provide enough time for physiological and psychological adaptations to occur, which may explain why some individuals do not show significant improvements. Therefore, it is essential to consider that interventions of longer duration may favor a more significant accumulation of physical benefits, such as increased endurance and muscle strength, as well as improvements in mental health, promoting more consistent and sustainable results over time [30].

The weekly frequency of aerobic exercise followed the recommendations of the ACSM [11], with 2 sessions a week for aerobic and muscle strength exercise. This number of weekly sessions favors adaptations that lead to catabolism followed by protein anabolism, allowing lean mass to be maintained or increased [30]. The sessions will last 90 min and will take place twice a week, with recovery periods of at least 48 h, and all interventions will be guided by a physical exercise technician (PET), a psychologist, and four monitors. As far as the type of exercises is concerned, one that focuses directly on the aerobic aspect is prescribed throughout the program and, as far as muscle strength is concerned, a circuit structure is used, recruiting the main muscle groups, taking into account its ease of execution and explanation, simplifying understanding on the part of the individuals. The number of sets varies between 1 and 3, according to the ACSM [11]. Some authors have stated that in untrained individuals, both single sets and multiple sets produce similar increases in upper and lower limb muscle strength, meaning that in the initial stages, strength training, regardless of the number of sets, seems to be effective in improving muscle results [30]. The number of repetitions per set ranges from 8 to 12. The intensity is progressive throughout the program, and the stimuli and loads imposed will be continually adjusted in order to trigger the consequent adaptation processes in the body, taking into account the principle of progressive overload. The program will initially be carried out at a moderate intensity, between 50% and 60% of HRM, progressing to a range of 60%-70% of HRM until reaching a vigorous intensity between 70% and 80% of HRM. In order to monitor the groups’ adherence to the sessions or to suspend the exercise if any participant reports abnormal pain, dizziness, vomiting, or other adverse events, a record sheet will be created to be filled in at each session, representing the only “non-exercise” component utilized during the intervention.

According to Li [31], there are a variety of practical intervention strategies to consider when implementing a PE program for individuals with ASD, as follows: (i) placing participants in a half-moon position whenever important information is provided; (ii) using a short, objective lecture, avoiding wasting useful practice time; (iii) using questioning; (iv) providing collective and individual pedagogical feedback (descriptive, evaluative and prescriptive), both auditory and visual; (v) completing the feedback cycle; (vi) adapting one’s tone of voice to the moment and the practitioner; and (vii) always using demonstrations. The management dimension includes the following strategies: (i) adapting the exercises individually; (ii) drawing up a logical sequence of execution; (iii) defining in advance the order in which the tasks will be carried out; (iv) preparing the material in advance; (v) using few materials; (vi) complying with the predefined timings at each moment of the session; (vii) reducing the transition time between exercises; (viii) asking the participants to help collect the material; and (ix) creating routines. As for the climate dimension, the following practices must be applied: (i) active circulation around the space; (ii) correct positioning in front of the participants; and (iii) an avoidance of dead time, which leads to distractions. Finally, we highlight the discipline dimension with the following practices: (i) reprimanding deviant and incorrect behavior and (ii) using eye contact, posture, and an appropriate image to capture the attention of the practitioners. Table 1 shows the details of the PE program.

